### **Non-inclusion criteria**

- Known HCV status with previous HCV treatment
- Severe disease present at inclusion involving life threatening

- Concurrent participation in any other clinical study without written agreement of the two study teams

## 7. STUDY ENDPOINTS

### Primary endpoint

The primary endpoint is the **combined-testing uptake** defined as the number of persons tested for HCV RDT AND HCV RNA and aware of their status among the total number of persons eligible residing in the region where the intervention takes place

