## 8. STRATEGIES AND TREATMENTS

### Strategies

#### Arm 1: Facility-based testing intervention

Community Health Workers (CHWs) will provide information on the possibility to be tested in health centers for HCV infection. Information will be provided using information sheet and a dedicated leaflet in the selected households. If the participant agrees to participate, she/he will receive a voucher to go to referral health center for testing. In health center, after signature of

consent form, HCV testing will be done using HCV RDT on a finger stick capillary whole blood. Results will be available in 15 minutes. In case of positive HCV RDT, an immediate blood sample collection (5 mL of whole blood on EDTA) will be done in health center and sent to Provincial hospital laboratory to collect plasma. Plasma will be sent to UHS to perform HCV RNA. Results will be sent back to the health center and nurses will be in charge to give result to the participant and to refer to care in case of active infection (systematic appointment + phone call if the participant doesn't come).

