### Arm 2: Community-based testing intervention

After a dedicated training, CHWs will do the HCV RDT on a finger stick capillary whole blood directly in the household of participant. Information will be provided by the CHW using information sheet and a dedicated leaflet. If the participant agrees to participate, the signed consent form will be collected at this step before any RDT collection. In case of structural or societal barriers for household testing, it will be possible to provide testing in a specific location in the village. The visits will be planned with the head of village and he will be in charge to inform the population. In case of absence of participant during the first visit, a second visit will be scheduled. In absence of participant during the second visit, no additional visit will be planned.

In case of positive HCV RDT, 5 blood spots will be collected immediately on DBS, put in a specific plastic bag with the ID number and sent to UHS (Rodolphe Merieux laboratory) for HCV RNA extraction and amplification. Results will be sent back to the referral health center of each village and nurses will be in charge to give result to the participant and to refer to care in case of active infection (systematic appointment + phone call if the participant doesn't come).

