### **Testing phase for Arm 1**

The testing phase for arm 1 will take place in health center. During this visit, the investigator:

- Check to confirm that 1/ the participant is in the list of selected HH (2) the number on the participant's voucher match with the second part.
- Check eligibility criteria
- Collect the written consent form
- Attribute a identification code in the study
- Complete the confidential list including personal information (address, phone number) and keep it in a secured cupboard in the health center
- Fill the screening form
- Perform the HCV RDT on a finger stick capillary whole blood
- Give the result to the participant
- Provide specific counseling to avoid future transmission in case of negative result

- Collect blood sample (5 mL EDTA tube) in case of positive RDT and send it to Provincial hospital laboratory to collect plasma. Plasma will be sent to UHS with the ID number to perform HCV RNA
- Give an appointment to participant to receive the result of HCV RNA

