### **Testing phase for Arm 2**

The testing phase for arm 2 will take place directly in the household of participant or in a specific location in the village. During this visit, the CHW:

- Check eligibility criteria
- Provide oral information, information sheet
- Collect the written consent form and give an ID number
- Complete the confidential list including personal information (address, phone number) and keep it in a secured cupboard
- Fill the screening form
- Perform the HCV RDT on a finger stick capillary whole blood
- Give the result to the participant
- Provide specific counseling to avoid future transmission in case of negative result
- Collect DBS (5 spots) on a finger stick capillary whole blood in case of positive RDT and put it in a specific plastic bag with the ID number
- Keep the DBS in HC in the fridge and send to UHS on a regular basis
- Give an appointment to participant to receive the result of HCV RNA

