## **14. STATISTICAL ANALYSES**

### **Calculation of number of patients needed**

The study will be powered to detect an increase of HCV combined-testing uptake from 60% in the facility arm to 80% in the community arm among subjects older than 40 years.

According to Cambodia DHS report 2014, the average rural household size is 4 persons and the proportion of persons aged more than 40 years old is 25%, the cluster size is so estimated to 50.

The following assumptions and definitions will be used for the sample size calculation:

- an intra-class correlation of 0.01
- significance level  $\alpha = 0.05$
- power  $(1-\beta) = 80\%$
- clusters size: 50
- Design effect: 1.5

When accounting for the above-mentioned assumptions, 300 patients will need to be screened for HCV RNA and so, 6000 individuals aged above 40 years old will need to be screened by RDT (5% of patients are expected to have a positive HCV Ab). With an estimated median testing uptake of 60-70%, if we want to reach 6000 participants screened, it would be necessary to propose testing to 8000 participants from 160 clusters (80 clusters per intervention).

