#### **Primary outcome**

The percentage, and its 95% confidence interval, of persons tested for HCV RDT AND HCV RNA and aware of their status among the total number of persons eligible residing in the region where the intervention takes place will be compared between the 2 arms.

An analysis stratified on age and province of location will also be performed.

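### The primary endpoint requires an RNA test that only RDT-positive persons receive, so it cannot exceed antibody prevalence and cannot take the planned 60% and 80%

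*Protocol*

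**What the plan says.** The endpoint is defined in the same way in three places: the Study Summary (Outcomes), section 7 (Primary endpoint) and section 14 (Primary outcome). Section 7 gives it as "the number of persons tested for HCV RDT AND HCV RNA and aware of their status among the total number of persons eligible" and residing in the intervention region. The analysis paragraph in section 14 repeats it: "persons tested for HCV RDT AND HCV RNA and aware of their status among the total number of persons eligible residing in the region".

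The testing pathway makes RNA conditional on the RDT in both arms.
- Section 8, Arm 1: "In case of positive HCV RDT, an immediate blood sample collection" follows. The Arm 1 steps in section 9 say the same: "Collect blood sample (5 mL EDTA tube) in case of positive RDT".
- Section 8, Arm 2: "In case of positive HCV RDT, 5 blood spots will be collected immediately on DBS". In the Arm 2 steps of section 9, the dried blood spots are taken "on a finger stick capillary whole blood in case of positive RDT".
- RDT-negative persons receive their result and counselling, and no RNA test is planned for them.

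Section 14 (Calculation of number of patients needed) states that the trial is "powered to detect an increase of HCV combined-testing uptake from 60% in the facility arm to 80% in the community arm" and that "5% of patients are expected to have a positive HCV Ab". It derives 300 persons screened for RNA, then 6,000 screened by RDT, then 8,000 offered testing in 160 clusters (80 per arm). The Study Summary repeats this calculation.

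**The concern.** The great majority of people who complete testing will be RDT-negative: 95% on the plan's own expectation. They have had every test the protocol offers and know their status, yet the endpoint as written counts them as not reached. The planned 60% and 80% are values that this endpoint cannot take.

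Two things are at stake. First, the definition and the sample size belong to different quantities, so the stated 80% power is not power for the stated endpoint. Second, the analyst will have to choose a workable reading. The all-eligible denominator points to one reading and the sample-size arithmetic to another. The two differ in denominator, estimand and power, and that choice should be fixed before results are seen.

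**Working it through.** **Inputs.** From section 14: uptake 60% and 80%; alpha 0.05 (sidedness not stated, taken as two-sided); power 80%; ICC 0.01; cluster size 50; design effect 1.5; antibody positivity 5%; 8,000 persons, so 4,000 per arm. From section 3 (HCV situation in Cambodia): prevalence that may reach 10 to 15% in persons over 50.

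**1. The plan's own figure.** For 60% versus 80%, two-sided 0.05, 80% power:
- Without continuity correction: 82 per arm; 82 x 1.5 = 123; total 246.
- With continuity correction: 91 per arm; 91 x 1.5 = 136.5, rounded up to 137; total 274.

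The stated 300 is not reproduced exactly, but it is not too small on its own premise: 150 per arm at design effect 1.5 gives 87.6% power. The point made here does not depend on this gap. The next step does reproduce: 300 / 0.05 = 6,000.

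**2. Which denominator that chain uses.** Dividing 300 by the antibody-positive fraction makes the 300 RDT-positive persons. The 60% versus 80% has therefore been applied to RDT-positives, not to all eligible residents. The design effect, however, is 1 + (50 - 1) x 0.01 = 1.49, which uses the full cluster of 50. RDT-positives number about 50 x 0.05 = 2.5 per cluster, for which the design effect would be 1 + 1.5 x 0.01 = 1.015. The paragraph thus mixes the two denominators.

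**3. Cap on the endpoint as written.**

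endpoint = P(RDT done) x P(antibody positive) x P(RNA done and result given)

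Its maximum is P(antibody positive): 5% on the planning figure, 10 to 15% at the highest cited prevalence. Reaching 60% or 80% would need at least that share of eligible residents to be antibody positive.

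**4. Value at the planned uptake.** Reading 60% and 80% as RDT uptake, with every RNA test done and disclosed:
- facility: 0.60 x 0.05 = 3.0%
- community: 0.80 x 0.05 = 4.0%

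**5. Power for 3.0% versus 4.0%.** With 4,000 per arm and design effect 1.49:

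z = 0.01 / sqrt[(0.03 x 0.97 + 0.04 x 0.96) x 1.49 / 4000] = 0.01 / sqrt(0.0675 x 0.0003725) = 1.99

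Power = Phi(1.99 - 1.96), about 51%. For 80% power, 5,301 per arm are needed before clustering. That becomes 7,899 at design effect 1.49, or 7,952 at 1.5 (15,904 in total).

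**6. Sensitivity to prevalence (illustrative, assumed values).** At 60% uptake and 6% positivity the endpoint is 3.6%; at 80% uptake and 4% positivity it is 3.2%. A chance difference in prevalence of that size would reverse the ranking of the arms. Section 5 (Study overview) allocates four geographic areas per province to the arms, eight in all, so some chance imbalance is plausible.

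**7. The endpoint read as testing completed as indicated.** With 60% versus 80% among 4,000 per arm and design effect 1.5, power is close to 100%.

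**The case against.** The best defence is that the intent is plain and that an analysis plan could put it into operation. The intent is not settled by the text. The denominator of all eligible residents suggests testing completed as indicated, while the step from 300 to 6,000 suggests RNA completion among RDT-positives. Neither is written down. The second would also condition on who came for testing, which is what the intervention is meant to change. Nor is this a detail left for later: the protocol fixes the unworkable form three times, once in its own analysis section.

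The schedule table in section 9 marks RNA at the testing phase without a condition, and its footnotes on those entries separate only the arms. Every procedural description states the positive-RDT condition, so the table does not rescue the definition.

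A reader might go further and infer that the endpoint measures prevalence rather than uptake and cannot test the hypothesis at all. The documents do not support that. At equal prevalence and RNA completion, 3.0% to 4.0% is the same ratio as 60% to 80%, so the contrast still tracks uptake. Allocation of areas is random, so prevalence differences are chance imbalance and not systematic bias. What is lost is power and robustness.

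A reader might also want power at the level of the eight areas. The protocol gives one ICC, for clusters of 50, and none for areas. Any such figure would rest on outside assumptions and concerns the unit of randomisation, a separate issue.

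**Conclusion.** The contradiction stands. The primary endpoint, the testing pathway and the 60% versus 80% planning values cannot all be right. As written, the endpoint is capped at antibody prevalence: 5% on the planning figure, higher if prevalence is higher, but nowhere near 60%. At the planned uptake it would be at most 3.0% versus 4.0%, tested with about 51% power instead of 80%, and open to distortion by chance prevalence differences between areas.

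The 51% assumes two-sided 0.05, 4,000 per arm, design effect 1.49, equal prevalence in both arms and complete RNA follow-through. The cap needs only the definition and the positive-RDT condition. This should be corrected before analysis.

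**What to change.** - **Endpoint.** In the Study Summary, section 7 and the Primary outcome paragraph of section 14, define the numerator as testing completed as indicated: RDT negative and told the result, or RDT positive with an RNA result and told that result. Keep the stated denominator of eligible persons residing in the area.
- **Sample size.** In the Study Summary and section 14, restate the basis on that denominator instead of on 300 RNA-tested persons. Otherwise the sample-size text would still contradict the new endpoint.
- **Data.** Record awareness of the result for RDT-negative persons too. Section 9 (Case detection phase) describes confirming awareness and completing the CRF only at the RNA-result visit. In Arm 1, eligibility is checked at the health centre, so state how eligible non-attenders are counted.
- **Reporting.** Give RNA completion and disclosure among RDT-positives as a descriptive cascade step.

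The cost is an amendment and a small addition to data capture. There is also a scientific cost. At 5% positivity the new primary differs from the secondary antibody-testing uptake only for RDT-positives without a communicated RNA result, at most 5% of those tested, so the two will be close. It still requires the RNA step for those who need it, in line with the package of serological and virological testing in section 3 (Study main hypothesis). The protocol should acknowledge the overlap.

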### Secondary endpoints

The following secondary endpoints will be measured and compared between the 2 arms:

- **HCV antibody testing uptake** defined as the number of persons tested for HCV RDT and aware of their status among the total number of persons eligible residing in the region where the intervention takes place
- **Active case detection rate** defined as the number of persons with HCV active infection (positive HCV Ab and positive HCV RNA) and results given and explained among the total number of persons eligible residing in the region where the intervention takes place
- **Linkage to care** defined as the number of persons with at least one consultation in the Provincial Hospital among the estimated total number of persons with active infection residing in the region where the intervention takes place

The following secondary endpoints will be measured for the total population and not compared:

- **Treatment uptake** defined as the number of people initiating HCV treatment among the total number of persons with active infection linked to care
- **Liver-related morbidity and mortality** (decompensated cirrhosis, HCC)
- Proportion of patients with sustained virologic response 12 weeks after discontinuation of treatment (**SVR12**)
- Proportion of patients with **treatment failure** defined as absence of SVR12 or missing HCV-RNA at 12 weeks post-treatment (PT12) due to treatment discontinuation for AEs or death

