### Secondary objectives

- To compare the HCV antibody testing uptake between the 2 arms for the eligible population
- To compare the active case detection rate between the 2 arms for the eligible population
- To compare the linkage to care between the 2 arms for those with active infection
- To compare the cost-effectiveness of the two strategies
- To evaluate the treatment uptake
- To evaluate the effectiveness and safety of a 12-week dual-therapy of direct-acting antiviral (DAA) treatment

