### **Visit W24**

HCV RNA will be performed to evaluate the SVR12. In case of cirrhosis, CBC, PT, bilirubin, albumin will be done to evaluate the Child score and liver ultrasound will be performed to screen HCC.

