### **Permanent study treatment discontinuation**

Reasons for permanent discontinuation of study treatment include:

- Willingness of the patient;
- Any medical event requiring discontinuation of the study treatment (drug-intolerance or occurrence of Serious Adverse Events (SAE), occurrence or worsening of a concomitant illness);
- Need for the patient to be treated with a non-authorized concomitant medication;
- Death of the patient;
- Non-adherence to the study treatment endangering the patient's health.

If a patient wishes to discontinue study treatment at any moment, investigators should explain the importance of remaining on study follow-up, or - failing this - of allowing routine follow-up data to be used for study purposes.

A premature discontinuation of study treatment must be notified by e-mail to the clinical study manager of the CTU as soon as the investigator is aware and reported in the patient CRF. The reasons and date of the discontinuation should be documented in the patient's medical file. Study treatment discontinuation should not lead to patient withdrawal from the study: patients discontinuing their study regimen have to be followed-up according to the scheduled study visits until the end of the study and all data should be collected (under the condition that informed consent has not been withdrawn). They should receive the best possible care given their health status and current best knowledge.

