### **Loss to follow-up**

When a patient who has not explicitly withdrawn consent does not show up for routine visits, the study team (nurses, counsellors...) will search for him/her by all the way available (phone call, mailing, home-based care team). The study team will contact the patient via phone call or home visit, as long as s/he consented to phone calls and/or home visits in the consent form and provided a phone number and/or home address during the study.

A patient who does not show up for a given scheduled visit will be considered lost-to-follow-up when his/her last contact with the study team (either at the clinic, via telephone, or at home) was recorded prior to the date of his/her last scheduled visit to the clinic as per the study protocol.

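### The treatment-failure definition leaves patients whose post-treatment RNA is missing for reasons other than adverse events or death unclassified, so failure can read low for an effectiveness objective

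*Protocol*

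**What the plan says.** Section 7 (Secondary endpoints), and in the same terms the Study Summary, list two virological outcomes of treatment. One is the "Proportion of patients with sustained virologic response 12 weeks after discontinuation of treatment". The other is the proportion with treatment failure, "defined as absence of SVR12 or missing HCV-RNA at 12 weeks post-treatment (PT12) due to treatment discontinuation for AEs or death". Both belong to the endpoints "measured for the total population and not compared". They serve the secondary objective "To evaluate the effectiveness and safety of a 12-week dual-therapy of direct-acting antiviral (DAA) treatment".

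Section 9 foresees other ways in which a patient can end without a result:
- Under Permanent study treatment discontinuation, the reasons for stopping include the patient's own wish, the need for a concomitant drug that is not permitted, and "Non-adherence to the study treatment endangering the patient's health". Patients who stop are still to attend their scheduled visits.
- Under Loss to follow-up, a tracing procedure is set out for the case "When a patient who has not explicitly withdrawn consent does not show up for routine visits", and a rule says when the patient "will be considered lost-to-follow-up when his/her last contact with the study team" predates the last scheduled visit.

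Under Visit W24, "HCV RNA will be performed to evaluate the SVR12". The study schedule and Section 10 plan no other HCV RNA once treatment has begun.

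Section 14 does not mention SVR12 or treatment failure. No section gives the denominator of either proportion.

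**The concern.** The failure definition contains a missing-data rule. By naming two causes that turn a missing result into a failure, it leaves out every other cause, including causes that Section 9 itself lists. Because week 24 is the only planned RNA after treatment starts, a patient who misses it has no other scheduled result from which the outcome could be read, and the rule alone decides where that patient goes. As written, the patient goes nowhere.

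Two things are at stake. First, the failure proportion answers a narrower question than the effectiveness objective asks, which concerns everyone given the treatment. Second, two analysts could report different failure and SVR12 figures from the same data, each in line with the text. The protocol cites SVR12 above 95% for this combination, so virological failures should be few and even a modest number of missing results could outnumber them.

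**Working it through.** The protocol gives no target, precision or dropout figure for these endpoints, so there is no planned figure to reproduce. The check has two parts.

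**Reading the definition.** It has two limbs: absence of SVR12, and RNA missing because treatment was stopped for adverse events or because of death. If the first limb covered everyone without a documented SVR12, the second would add nobody. For the second limb to have any effect, the first must mean a measured non-response. The patients then fall out as follows:

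| Patient | SVR12 | Failure |
|---|---|---|
| RNA measured at week 24, response | yes | no |
| RNA measured at week 24, no response (including those who stopped early) | no | yes |
| RNA missing, stopped for adverse event, or died | no | yes |
| RNA missing, lost to follow-up | unclassified | unclassified |
| RNA missing, stopped by choice, for non-adherence or for a disallowed drug | unclassified | unclassified |

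**Size.** Inputs:
- Persons tested for RNA: 300 (Section 14).
- RNA-positive share: 262/372 = 70.4% (Section 3, an HIV cohort, used only to give a number of patients).
- Treated: N = 300 × 262/372 = about 211, assuming every active case is linked to care and treated.
- SVR12 among those tested: s = 0.95 (Section 3 reports above 95%).
- Loss: l = 0 to 20%, assumed, because the protocol gives none.
- Adverse-event discontinuation and death: set to 0.

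Formulas:
- Failure as written, over all starters: (1 − l)(1 − s).
- Failure with every missing result counted: 1 − (1 − l)s. The difference between the two is exactly l.
- SVR12 with lost patients excluded: s. SVR12 over all starters: (1 − l)s.

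| Loss | Lost of 211 | Failure as written | Failure, missing counted | SVR12, lost excluded | SVR12, all starters |
|---|---|---|---|---|---|
| 0% | 0 | 5.0% | 5.0% | 95.0% | 95.0% |
| 5% | 11 | 4.75% | 9.75% | 95.0% | 90.25% |
| 10% | 21 | 4.5% | 14.5% | 95.0% | 85.5% |
| 20% | 42 | 4.0% | 24.0% | 95.0% | 76.0% |

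If lost patients also leave the failure denominator, failure is 5.0% in every row. The percentages do not depend on N.

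Changing the other assumptions leaves the gap as it is. At 10% loss, failure is 9.0% against 19.0% with s = 0.90. With s = 0.95 and 2% stopped for adverse events or dead, it is 6.4% against 16.4%.

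The failure-as-written column equals the rate if every lost patient were cured, and the missing-counted column equals the rate if none were. The true rate lies between them.

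**The case against.** A reader might infer that the plan overstates the effectiveness of the treatment. The text does not support that as a firm conclusion. SVR12 is a separate endpoint with no exclusion written into it. If its denominator is all treated patients, those lost already count against it and nothing is overstated. The contrast of 95.0% with 85.5% at 10% loss is therefore conditional on a denominator that the protocol does not state and that a SAP, not shown here, may settle.

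A reader might also call this a per-protocol analysis. It is not one: patients who stop early stay in follow-up, and if their week-24 RNA is measured they are classified by it whatever the reason for stopping. Only stoppers whose RNA is also missing are affected. The tracing by phone, mail or home visit should also reduce the number lost.

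Nor is the direction of bias against the truth established. The last drug delivery is at week 8 and the RNA is at week 24, so someone lost late may have completed the course and been cured. Counting all missing results as failure is a conservative convention, and some lost patients would be misclassified by it.

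These arguments limit the point but do not remove it. The failure rule is stated in the protocol, and it picks out some causes of missing results and omits others that the protocol foresees. A broader reading of the first limb is possible only by making the second redundant, and that ambiguity would itself need correcting.

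**Conclusion.** The point holds in limited form. On the natural reading of the definition, a week-24 RNA missing for any reason other than discontinuation for adverse events or death leaves the patient unclassified. The failure proportion over all starters is then lower than under a missing-as-non-response rule by exactly the share of such patients: 5 to 20 percentage points at assumed losses of 5% to 20%, and zero if nobody is lost. Whether SVR12 is affected depends on its unstated denominator. The loss rates are assumptions. The 95% comes from the cohort cited in the rationale.

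The severity is minor. The endpoint is secondary, descriptive and pooled over arms, and the primary comparison, its power and its significance level are unaffected.

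**What to change.** In Section 7 and the Study Summary:
- Define both SVR12 and treatment failure over all patients who started DAA.
- In the main analysis, count any missing RNA at 12 weeks post-treatment as not achieving SVR12, whatever the cause, so that the two proportions sum to 100%.
- Keep the current failure definition as a sensitivity analysis, with its denominator stated.
- Report measured virological failure separately from missing or lost, with numbers by reason.

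This changes wording only and needs no further visits, samples or patients. The price is a less favourable headline that may be conservative, because some lost patients may be cured. Reporting the components separately lets readers see how much of the failure figure is missing data.
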